## Abstract

**Introduction:**

Intermittent neurogenic claudication (INC) is often caused by lumbar spinal stenosis (LSS). Laminectomy is considered a frequently used surgical technique for LSS. Previous studies have shown that laminectomy can potentially cause lumbar instability. Less invasive techniques, preserving midline structures including the bilateral small size interarcuair decompression, are currently applied. Due to lack of evidence and consensus, surgeons have to rely on their training and own experiences to choose the best surgical techniques for their patients. Hence, an observer and patient blinded multicentre, randomised controlled trial was designed to determine the effectiveness and cost-effectiveness of bilateral interarcuair decompression versus laminectomy for LSS.

**Methods and analysis:**

174 patients above 40 years with at least 12 weeks of INC will be recruited. Patients are eligible for inclusion if they have a clinical indication for surgery for INC with an MRI showing signs of LSS. Patients will be randomised to laminectomy or bilateral interarcuair decompression. The primary outcome is functional status measured with the Roland-Morris Disability Questionnaire at 12 months. Secondary outcomes consist of pain intensity, self-perceived recovery, functional status measured with the Oswestry Disability Index and a physical examination. Outcome measurement moments will be scheduled at 3 and 6 weeks, and at 3, 6, 12, 18, 24, 36 and 48 months after surgery. Physical examination will be performed at 6 weeks, and 12, 24 and 48 months. An economic evaluation will be performed and questionnaires will be used to collect cost data.

**Ethics and dissemination:**

The Medical Ethical Committee of the Erasmus Medical Centre Rotterdam approved this study (NL.65826.078.18). The results will be published in an international peer-reviewed journal.

**Trial registration number:**

ClinicalTrials.gov (NCT03480893).

**IRB approval status:**

MEC-2018-093.

Strengths and limitations of this studyPatient and observer blinded randomised controlled design.Both patient-reported outcomes and objective functional test outcomes will be measured.Inclusion of an economic evaluation.Instability as outcome may not be measurable in 2 years of follow-up.Diversity in terminology on posterior decompression techniques may lead to variability on both surgical techniques.

## Introduction

Lumbar spinal stenosis (LSS) is described as the narrowing of the diameter of the spinal and nerve root canals, which can cause compression of the neural structures in the canals.^1^ LSS is a common medical condition in the ageing population and is considered the most common reason for lumbar spine surgery for people over the age of 65.^2–4^ Intermittent neurogenic claudication (INC) is the most important symptom of LSS, with leg pain and heaviness of the legs, usually bilateral, which exacerbate during standing and walking. Apart from leg pain, back pain is often also present.^5^ As the symptoms aggravate, the ability to walk can become considerably limited, which is the dominant functional impairment and the most common reason for seeking medical care.^6 7^

Conservative treatment, such as physical therapy and pain medication, is the first treatment option and may give some relief of symptoms.^8^ Previous research shows that there is sparse evidence of the effectiveness of surgery compared with non-operative treatment.^9^ However, usually when conservative treatment fails, surgical treatment is considered the next option.^10 11^ The first technique described to widen the lumbar spinal canal is the laminectomy technique, also known as wide bony decompression, which is a widely used surgical technique for patients with INC caused by LSS.^12^ Given that patients often experience postoperative back pain after laminectomy, it is hypothesised that laminectomy is a ground for potential lumbar instability and iatrogenic scoliosis.^13–15^ Performing a procedure with potentially more complications in an elderly population could be considered as doubtful. Hence, less invasive techniques, such as the bilateral small size interarcuair decompression, otherwise known as a bilateral laminotomy, limited bony decompression or interlaminar decompression, were developed and implemented in clinical practice. These techniques require less bone tissue to be removed, which possibly can reduce the prevalence of lumbar instability in these patients and consequently improve functioning.^16^ Furthermore, it is believed that, compared with laminectomy, these less invasive techniques have the ability to decompress the nerves while preserving the spinal integrity. However, the risk of an insufficient decompression may be higher, possibly resulting in reoperations due to residual stenosis.^16–18^

The presumption is often made that, after a wide decompression, recurrence of the complaints is scarce. The opinions on this matter are diverse and subject to debate.^19^ Therefore, a randomised controlled trial (RCT) is needed to clarify whether bilateral interarcuair decompression is effective and cost-effective compared with a classical laminectomy.

### Study objectives

The primary objective of this study is to determine whether bilateral interarcuair decompression is more effective than laminectomy in patients with INC caused by LSS. The secondary objective is to evaluate if bilateral interarcuair decompression is more cost-effective than laminectomy.

### Study design

The study is designed as a multicentre, patient and observer blinded RCT with an economic evaluation alongside. Participants will be allocated to one of the two groups: laminectomy or interarcuair decompression.

## Methods

### Study setting/population

In total 174 patients with an MRI-confirmed LSS will be recruited. All patients who will be included should have an indication for surgery due to LSS with minimally 12 weeks of INC, as is customary in clinical practice, and failed conservative treatment. Patients will be recruited from two hospitals and one private health clinic in the Netherlands:

Erasmus Medical Centre (MC) in Rotterdam.Maasstad Hospital in Rotterdam.Park MC in Rotterdam.

### Eligibility criteria

In order to be suitable to participate in this study, patients must meet all of the following criteria:

#### Inclusion criteria

At least 12 weeks of INC with a leg pain level above 3 on a Numeric Rating Scale (NRS), without sufficient response to conservative management.Indication for an operation according to consensus of surgeon.MRI demonstrating LSS.Age above 40 years.Sufficient knowledge of the Dutch language in order to comprehend the questionnaires and patient information.Written informed consent.

#### Exclusion criteria

Patients who meet any of the following criteria will be excluded from participating in this study.

History of lumbar spine surgery.More than two lumbar levels needing surgery.Degenerative spondylolisthesis greater than Meyerding grade I (on a scale of I–V).^20 21^
Concomitant scoliosis or disc herniation.Severe comorbid medical disorder (American Society of Anesthesiologists >3).Serious psychopathological disorder.Pregnancy.Active malignancy.Plans to move abroad during study period.

Eligible patients will be randomised in a 1:1 ratio to the two groups.

### Interventions

#### Intervention: bilateral small size interarcuair decompression

The intervention consists of the interarcuair decompression, otherwise known as a bilateral laminotomy, limited bony decompression or an interlaminar decompression. General anaesthesia is to be administered. A midline skin incision is made, after which the paravertebral muscles are dissected subperiosteally and retracted bilaterally. Decompression will be applied through decompression of the ligamentum flavum and partial laminotomy if necessary. The lateral recess will be opened bilaterally and a partial medial facetectomy will be performed to decompress neuronal structures including the exciting nerve root. The lamina will be removed up to the ligamentum flavum. Interspinous ligaments are spared.^22^ The wound is closed in layers. Patients are operated with a loupe magnification or microscope depending on the surgeon’s preference.

#### Control group: conventional laminectomy

The control group consists of conventional laminectomy, otherwise known as wide bony decompression. General anaesthesia is to be administered. A midline skin incision is made over the spinous processes. The laminae of the affected level(s) are exposed subperiosteally, and the supraspinous ligament is incised. The spinous process is removed. The supraspinous and interspinous ligament of the affected level is removed by drill or Kerrison punched. Both laminae are removed at the affected level, leaving the facet joint intact. The lateral recess is opened bilaterally and a partial medial facetectomy will be performed to decompress neuronal structures including the exciting nerve root.^16^ To clarify, when a single level stenosis is present (eg, L4–L5), both laminae L4 and L5 will be removed. When a double level stenosis (eg, L3–L4 and L4–L5) is present, three laminae (L3, L4 and L5) will be removed. The wound is closed in layers with or without a suction drain. Patients will be operated with loupe magnification or microscope depending on the surgeon’s preference.

#### Use of co-intervention

Pain medication will be provided to patients after surgery, should this be necessary. Further, the use of co-interventions will be tracked by cost questionnaires, in which medication usage and any healthcare utilisation is monitored throughout the follow-up period.

### Outcomes

#### Primary outcomes

The primary outcome is a functional status measured using the Roland-Morris Disability Questionnaire (RMDQ). This is a 24-point questionnaire that is designed to assess the functional status in patients with low back pain. This outcome measure has been identified as one of the most commonly used outcomes in a population with chronic low back pain.^23–27^

#### Secondary outcomes

##### Oswestry Disability Index

The Oswestry Disability Index (ODI) is one of the principal condition-specific outcome measures used in the management of spinal disorders.^28^ The current V.2.1a will be used.^29^ It consists of 10 questions, each with 6 possible answers and each answer option receives a score of 0–5 points, yielding a score range between 0 and 50, which is scaled to a 100% range. The questions focus on a range of daily physical functions and how the back or leg pain is affecting the patient’s ability to manage in everyday life.

##### NRS for leg and low back pain

This parameter will measure the experienced pain intensity in both legs (affected and non-affected) and back. Pain intensity will be rated on an 11-point scale, varying from 0 representing ‘no pain’ to 10 ‘the most terrible pain imaginable’. Patients are not permitted to see the pain score indicated during previous visits. Reliability and validity of NRS have been shown.^30^

##### Short form 36

The quality of life will be measured with the Dutch version of the Short Form 36 (SF-36). The SF-36 has been applied and successfully validated in populations with low back pain.^31^ This questionnaire relates to the analysis of the general functional status of the patient. The questionnaire is divided into eight health concepts: (1) physical functioning, (2) role limitations because of physical health problems, (3) bodily pain, (4) social functioning, (5) general mental health (psychological distress and well-being); (6) emotional role limitations; (7) vitality and (8) general health perceptions. The scores of the different health concepts are added up into a scale of 0–100. A higher score reflects a better general health condition. The physical and mental component summary will be assessed separately.

##### Patients’ perceived recovery

Recovery will be measured using a 7-point Likert scale. The score on this scale varies from ‘complete recovery’ to ‘worse than ever’. The outcomes ‘complete recovery and ‘almost complete recovery’ will be dichotomised and considered as recovered.^32^

##### Patients’ satisfaction

Patients’ satisfaction of change and satisfaction of treatment will be assessed using a 7-point Likert scale, ranging from ‘completely satisfied’ to ‘completely dissatisfied’. ‘Completely satisfied’ and ‘almost completely satisfied’ will be defined as good outcome.

##### Physical examination

A physical examination will be performed before surgery, at 6 weeks, 12, 24 and 48 months after surgery. This examination will include a brief neurological examination, the Timed Up and Go Test (TUG), the Timed Chair-Stand Test (TCST), the 6-Minute Walking Test (6MWT) and patient’s weight.

Neurological examinationThe neurological examination will include the muscle strength of the quadriceps, the iliopsoas, the hamstrings, the gastrocnemicus and the tibialis anterior muscle, which will be noted as a difference in strength between both legs. We will evaluate if there is a difference in muscle strength between the affected leg and the other leg.TUGPatients are asked to sit in a chair with their arms resting on the armrests. On direction of the research nurse, patients have to walk as fast as possible (without running) to a wall at 3 m distance of the chair. When they have reached that wall, a turn of 180° is made and they walk directly back to the chair and sit down. The research nurse will measure the time(in seconds) it takes for a patient, to perform this action. The time is stopped when the patients are seated again.^33^ Patients need to perform this test, three times. Patients are allowed to wear their regular shoes and use a walking aid, if necessary. The TUG test has been described as a valid, reliable tool in the assessment of objective functional impairment in patients with lumbar degenerative disc disease.^34 35^ However, this has not been done for LSS. The validation for LSS will be conducted in this study.TCSTPatients are asked to sit down on an armless chair, firmly placed against a wall, with their arms folded across their chest. They are instructed to place their feet flat on the ground. To become familiarised with the exercise, the patients are asked to stand up and sit down again without using their arms. If assistance is required during this action, or this movement cannot be completed by the patient, the test is abandoned. If the manoeuvre is possible, the patient will be asked to, on the word ‘go’, stand up entirely and sit down again, five times as quick as possible. The research nurse will time the five movements in seconds from the command ‘go’ to the completed fifth stand. The measured time will be noted as the score. If the patient is unable to perform the test five times, a maximum score will be noted of 30 s.^36^
^37^
6MWTThis test is performed to assess the gait pattern, walking speed and physical endurance of patients. The patient will be requested to walk at such a speed that at the end of 6 min, the patient will have the feeling of maximum output.^38^ Before taking the test, the patient will be given the instructions to install the 6MWT application on their cell phone.^39 40^ During these 6 min this application will measure the walking distance. During the walking test, the patient is permitted to use a walking aid and/or orthosis which will be noted.

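### Recording muscle strength only as a between-leg difference cannot show equal weakness in both legs; separately, two chair-stand scoring sentences need reconciling

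*Protocol article*

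**What the plan says.** **Strength.** Under Physical examination, the neurological examination covers five muscle groups (quadriceps, iliopsoas, hamstrings, gastrocnemius, tibialis anterior). The result is a single comparison per muscle, "which will be noted as a difference in strength between both legs". The stated purpose is the same within-patient contrast: "We will evaluate if there is a difference in muscle strength between the affected leg and the other leg". No grade for each leg is mentioned. The examination takes place before surgery, at 6 weeks and at 12, 24 and 48 months.

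**Laterality.** The Introduction describes intermittent neurogenic claudication "with leg pain and heaviness of the legs, usually bilateral, which exacerbate during standing and walking". The interarcuair operation treats both sides ("The lateral recess will be opened bilaterally and a partial medial facetectomy will be performed"), and the laminectomy section also has the lateral recess opened on both sides.

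**Chair-stand test.** The patient first tries one practice stand: "If assistance is required during this action, or this movement cannot be completed by the patient, the test is abandoned". That sentence gives no score. If the practice stand succeeds, five stands are timed and the time is the score. The description ends: "If the patient is unable to perform the test five times, a maximum score will be noted of 30 s".

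**Analysis.** The Statistical analysis section lists the chair-stand test among the exploratory secondary outcomes for mixed models. It names no analysis for the neurological examination, and it allows multiple imputation where necessary.

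**The concern.** A between-leg difference makes sense when one leg is diseased and the other serves as its control. Here the protocol's own account of the disease and both of its operations involve both sides, so the second leg is not a reliable reference. The difference says how unlike the legs are, not how weak the patient is. At stake is whether the neurological outcome can show deficit, recovery or harm when both legs are involved. This rule governs what is written on the form. If it is followed as written, the grades for each leg are never stored, and an analysis plan cannot recover them.

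The chair-stand issue is one of scoring. If an abandoned test carries no score, the patients who performed worst are missing because of their inability, while slightly better performers count as 30 s. The text leaves open whether that happens.

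**Working it through.** The protocol gives no figure on either point, so there is none to reproduce.

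**Strength: what the difference can and cannot show.** The protocol names no strength scale. For illustration, assume a grade from 0 to 5 (5 = normal) and define D = grade of the other leg − grade of the affected leg.

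| Affected / other | D | True state |
|---|---|---|
| 5 / 5 | 0 | normal |
| 4 / 4 | 0 | mild weakness, both legs |
| 2 / 2 | 0 | marked weakness, both legs |
| 4 / 5 | 1 | one mildly weak leg |
| 2 / 3 | 1 | two clearly weak legs |

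D does not separate the first three rows from each other, or the last two. Changes over time also mislead:

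- 4/5 to 4/4: D goes from 1 to 0. The stronger leg has acquired a deficit, and the record looks like improvement.
- 4/4 to 4/5: D goes from 0 to 1. One of two weak legs has recovered, and the record looks like worsening.
- 4/4 to 5/4: D goes from 0 to −1 (absolute value 1). That is the same change as 5/5 to 5/4, which is a new deficit, so keeping the sign does not resolve the ambiguity.

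This follows from subtraction alone and does not depend on the scale. How often it occurs cannot be computed, because the protocol gives no frequency of weakness in one or both legs.

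**Chair stand: the two sentences side by side.** *In sequence*, the 30 s sentence belongs to the timed test, which starts only after a successful practice stand. A patient who then fails gets 30 s; one who fails the practice stand gets nothing. *Literally*, someone who cannot stand once is also unable to do five stands and gets 30 s. Both readings fit the text, and staff at the three recruiting centres could apply different ones.

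The effect on the mean can be sketched only with assumed inputs: completers average m seconds in both arms, and proportions pL (laminectomy) and pI (interarcuair) are unable.

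- Unable patients left out: difference = m − m = 0 (forced by the assumption of equal completer means).
- Unable patients scored 30 s: difference = (pI − pL) × (30 − m).

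| m | pL / pI | Difference if scored 30 s |
|---|---|---|
| 18 s | 2% / 1% | (0.01 − 0.02) × 12 = −0.12 s |
| 15 s | 10% / 5% | (0.05 − 0.10) × 15 = −0.75 s |
| 12 s | 15% / 5% | (0.05 − 0.15) × 18 = −1.8 s |

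With 87 patients per group (Sample size section), the middle row is 0.10 × 87 = 8.7 against 0.05 × 87 = 4.35 patients. The table shows direction and order of magnitude under assumptions; it is not an estimate for this trial.

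**The case against.** **On strength.** The bilateral wording in the Introduction concerns pain and heaviness, not weakness, and eligibility rests on leg pain rather than motor deficit. The protocol does not show that symmetric weakness is common. No analysis of the difference as a severity score is named, so the misread changes are possible rather than planned. Nerve root damage and progressive neurological deficit are also collected as complications, and function is measured by several questionnaires and walking tests. All of this stands, and it keeps the point small. It does not rescue the recording rule: the systematic complication assessment is made shortly after discharge, whereas the examination continues to 48 months, and grades that were not stored cannot be rebuilt.

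**On the chair stand.** A reader might infer that patients who cannot stand once are definitely dropped, and that a slow completer can rank below someone who failed. The text supports neither as settled. The 30 s rule can be read to cover an abandoned test, and calling 30 s a maximum can be read as a cap. What remains is ambiguity. The proposed multiple imputation would not by itself resolve it, since it would treat inability as ordinary missing data.

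**On leg pain.** A reader might extend the argument to the pain scale, which covers "experienced pain intensity in both legs (affected and non-affected) and back". That does not follow. A score is kept for each leg, one leg may be worse even when both hurt, and the choice of leg to analyse is commonly left to the analysis plan.

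**Conclusion.** The strength point holds on the wording alone. A between-leg difference cannot tell symmetric weakness from normal strength, and it can reverse the apparent direction of change when the second leg is involved. The number of patients affected is unknown. It would be too strong to say that the rule hides the most impaired patients: the protocol does not link symmetric weakness to overall severity, and any size of shared deficit, mild or marked, gives 0.

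The chair-stand point is secondary: two sentences that must be reconciled. If abandoned tests carry no score, the loss from the mean difference is about 0.1 to 1.8 s under the assumptions shown, all of which lie outside the protocol. The outcome is exploratory.

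Neither point touches the Roland-Morris primary endpoint or the sample size. This is a low-severity improvement, worth making mainly because unrecorded strength grades are lost for good.

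**What to change.** **Strength.** Record the grade of each of the five muscles for each leg at every examination. Compare the treatment groups on the weaker-leg grade and on any new deficit since intake. The between-leg difference can still be derived. The cost is form fields only: 5 muscles × 2 legs = 10 entries instead of 5, so 5 more at each of 5 examinations, or 25 per patient. No visit or test is added. For examinations already done, grades should be retrieved from source notes where they exist.

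**Chair stand.** State that the 30 s score also applies when the test is abandoned at the practice stand, and that completers are capped at 30 s. Inability then does not enter the mixed model as ordinary missing data. Report the proportion unable by group. The cost is one or two scoring sentences and one form field; the small loss is detail among completers slower than 30 s.

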##### Complication and reoperation incidence

Immediately after surgery, the surgeon will report any perioperative complications such as cerebrospinal fluid leakage, nerve root damage and if the operation was implemented at the wrong vertebral level. Additionally, a systematic assessment of complications (including urinary tract infection, progressive neurological deficit and secondary bleeding) will be carried out by the surgeon and the research nurse shortly after discharge.

Reoperation is considered a bad outcome. The incidence of reoperation as well as perioperative morbidity will be assessed in both groups, using surgical parameters such as blood loss, time of surgery and length of hospital stay.

We used the Standard Protocol Items: Recommendations for Interventional Trials checklist when writing our report.^44^

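### Muscle strength is noted only as a between-leg difference although leg symptoms are usually bilateral and both operations decompress both sides, so change shared by both legs is not registered

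*Protocol article*

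**What the plan says.** Under Physical examination, the protocol article schedules a brief neurological examination before surgery, at 6 weeks, and at 12, 24 and 48 months. Strength is tested in the quadriceps, iliopsoas, hamstrings, gastrocnemius and tibialis anterior, "which will be noted as a difference in strength between both legs". The next sentence gives the evaluation: "We will evaluate if there is a difference in muscle strength between the affected leg and the other leg". The article mentions no strength value per leg and names no grading scale.

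Three other places bear on whether the second leg can serve as a reference:

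- The Introduction describes intermittent neurogenic claudication as presenting "with leg pain and heaviness of the legs, usually bilateral, which exacerbate during standing and walking".
- For the interarcuair decompression: "The lateral recess will be opened bilaterally and a partial medial facetectomy will be performed to decompress neuronal structures".
- For the laminectomy: "The lateral recess is opened bilaterally".

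Pain is handled differently. The section on the NRS has pain rated in both legs, affected and non-affected, as well as the back.

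**The concern.** A within-patient contrast between legs is a good measure when one leg is diseased and the other is a healthy control. In this trial the symptoms usually involve both legs and both treatments act on both sides. Benefit and harm can therefore appear in both legs, and the part they share cancels in the difference.

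At stake is what the strength examination can say about a limited versus a wide decompression. The Introduction raises insufficient decompression and residual stenosis as the possible price of the limited technique. If motor recovery or late motor loss differed between arms in a way common to both legs, the recorded value would tend not to show it, and a report of no difference in muscle strength would be weaker evidence than it appears. If only the difference is stored, an analysis plan cannot repair this later, because two values cannot be rebuilt from their difference.

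**Working it through.** The article states no sample size, power or rate for muscle strength, so there is no figure to reproduce. The check is algebra on the recorded quantity.

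**Inputs.** The recording rule and the evaluation rule come from Physical examination. The 0–5 grade per leg used below is an assumption for illustration.

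**Formula.** Let S1 and S2 be the strength of one muscle in the two legs. The recorded value is D = S1 − S2. The article does not say whether D is signed or absolute; |D| is shown below. If both recorded strengths change by the same amount c:

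D after = (S1 + c) − (S2 + c) = S1 − S2 = D before, for any c.

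**Numbers (leg 1, leg 2).**

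| Course | Before → after | Difference | Sum of both legs |
|---|---|---|---|
| Both weak legs recover | (4,4) → (5,5) | 0 → 0 | 8 → 10 |
| Both legs deteriorate | (5,5) → (4,4) | 0 → 0 | 10 → 8 |
| Both stay weak | (4,4) → (4,4) | 0 → 0 | 8 → 8 |
| One of two weak legs recovers | (4,4) → (4,5) | 0 → 1 | 8 → 9 |
| The better leg worsens | (4,5) → (4,4) | 1 → 0 | 9 → 8 |
| The single weak leg recovers | (4,5) → (5,5) | 1 → 0 | 9 → 10 |

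**Reading.**

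1. In the first three rows the difference is 0 throughout, although the courses are recovery, deterioration and no change.
2. In the fourth and fifth rows the difference moves the wrong way: an improvement looks like a new deficit, and a deterioration looks like recovery.
3. In the last row, the truly one-sided case, the difference behaves as intended. The rule is therefore not useless; it suits one-sided weakness.

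The sum separates all three courses in the first three rows and moves in the correct direction wherever strength changes. It needs both leg values, from which the difference can still be derived.

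**The case against.** **The bilateral premise concerns symptoms, not weakness.** The Introduction speaks of pain and heaviness, and opening both recesses describes surgical access. Nothing in the article says that motor deficits are symmetric or common, and both the pain and the strength sections work with an affected leg and another one. This stands. It is why the conclusion is that the other leg is not a *reliable* reference, not that it is usually weak.

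**A reader might infer that symmetric motor loss would go unseen by the trial.** The article does not support that. Under Complication and reoperation incidence, the surgeon reports nerve root damage directly after surgery, and the systematic check shortly after discharge includes "progressive neurological deficit and secondary bleeding". Table 1 records revisits and complications whenever they occur, and the section on ancillary care has adverse events monitored. Specific complications of interest are compared between groups by χ² or Fisher's exact tests. The TUG, TCST and 6MWT also reflect leg function at the same visits, though not strength per muscle or per leg.

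**A reader might infer that the arms cannot be compared on motor recovery at all, or that power collapses to the false-positive rate.** The first is too absolute, because asymmetric change remains measurable. The second depends on invented inputs. With 69 per arm, an assumed benefit of 0.5 SD in each leg, a between-leg correlation of 0.3 to 0.7 and an unbounded scale, power is 89–96% on the mean of the legs and about 5% on the difference. On an assumed 0–5 scale with a ceiling, the absolute difference reaches about 17–54% against 56–92% for the mean of the legs, and only the signed difference stays near 5%. Values per leg do better in each setting, but none of these figures measures the defect.

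**Strength carries little weight in the plan.** It is missing from the secondary outcomes named for mixed modelling (ODI, NRS, TUG, TCST, SF-36). At most it enters through the general reference to secondary outcome parameters at 24 to 48 months. Secondary outcomes are exploratory, and no objective or sample size rests on strength. This stands and sets the size of the point.

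**The case report form may hold a grade for each leg.** It is not shown, and the sentence may describe how results are expressed. That lowers certainty about permanent loss, but both the recording rule and the evaluation rule are explicit, so the text as written needs correcting.

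**Conclusion.** The point holds as a minor fault in one component of a secondary examination. Followed as written, the rule does not register strength change shared by both legs, and it can show recovery of one of two weak legs as a worsening. This follows from the definition of a difference and needs no assumption about effect size or scale. How often it matters depends on how often weakness or its recovery involves both legs, which the article does not state.

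Asymmetric change is still captured, neurological complications have their own route of capture, and the primary RMDQ comparison at 12 months is untouched. Whether strength per leg is lost for good depends on a case report form that is not available here.

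**What to change.** Replace the recording sentence with one stating that strength is recorded for each of the five muscles in each leg separately at every examination. Derive the between-leg difference from these values and keep it as a description. Compare the arms on the weaker leg or on the sum of both legs, adjusted for the same value before surgery, and state which of the two is used.

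The cost is one extra field per muscle: 5 more per examination, or 5 × 5 = 25 more per patient over the five scheduled examinations. Both legs must already be tested to obtain a difference, so there is no added procedure or patient burden. If the case report form already holds values per leg, correcting the protocol text and adding a sentence to the analysis plan is enough.
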